## Methods

### Study Design and Study Aims

The THRIVE Study is a two-armed RCT designed to evaluate the effects of GRIT, a psychoeducational health coaching intervention aimed at preventing the early initiation of regular alcohol and cannabis use in adversity-impacted adolescents ages 11 to 14 who are at high risk for toxic stress. This study will include two groups: an intervention group receiving the GRIT intervention and an active control group receiving a digital literacy curriculum. The study will assess the impact of the GRIT intervention on self-regulation and substance use outcomes through repeated measures at pre-intervention, post-intervention (2 months post-baseline), 6-month follow-up (8 months post-baseline), and 12-month follow-up (14 months post-baseline).

There are two specific aims for this study: (1) test the efficacy of GRIT on preventing the early initiation of regular alcohol and cannabis use among adversity-impacted adolescents ages 11–14 years who do not regularly use these substances at baseline; and (2) test the mediating effects of youth and caregiver self-regulation on the relationship between the GRIT program and adolescent substance use outcomes. A digital literacy active control group will allow for comparison in youth and caregiver outcomes. We hypothesize that adolescents who receive GRIT will have lower rates of regular alcohol and cannabis use compared to those in the active control group post-intervention, and that youth and caregiver self-regulation will mediate the relationship between the GRIT intervention and youth outcomes.

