### Power and Sample Size

We used the General Linear Mixed Model Power and Sample Size (GLIMMPSE) application to estimate the sample size needed for this study using the approach for longitudinal data (29). We calculated the sample size needed to detect a 40% lower change in use across time among the GRIT versus active control arm for both outcomes, as the Strengthening Families Program cited 50% reductions (30). In addition, we judged that a 40% reduction in initiation rate would be needed for a clinically meaningful effect. Given that exposure to four or more ACEs is associated with a two-to three-fold increase in early initiation (i.e., before age 14) of alcohol and cannabis use and national high school samples report initiation of alcohol before 13 to be 15% and cannabis to 5%, we conservatively assumed a 20% initiation for alcohol and 8% for cannabis for our high-risk study population (31–34). We also accounted for 20% attrition during the 14-month follow-up period and a variance inflation factor of 1.4 to accommodate the mediation analysis. Under these assumptions, a sample size of 105 dyads per arm (total N = 210 dyads) would be needed to provide 80% power at a nominal alpha of 0.025 for each outcome (adjusted for multiplicity to achieve an overall alpha of 0.05 for both outcomes). Previous research, such as the Support to Reunite, Involve, and Value Each Other (STRIVE) study and its adaptation, STRIVE +, has informed the sample size for this study. STRIVE evaluated a 5-session dyadic psychoeducational intervention with youth experiencing homelessness, enrolling 151 youth with a retention rate of 77% at a follow-up (3, 6, and 12 months) (35). STRIVE demonstrated efficacy in significantly reducing substance use, sexual risk, alcohol use, and illicit drug use over 12 months compared to the control condition. Given these findings, family based-interventions like GRIT may similarly reduce substance use and improve overall health and well-being. The findings from STRIVE+ further informed the design of our study, particularly highlighting the need for additional sessions and booster sessions. In STRIVE+, parents requested more sessions to practice newly acquired skills, as they experienced difficulties with familial connection. Based on STRIVE’s successful retention and outcomes, we believe that a sample size of 210 dyads (N=420) for the GRIT study is reasonable, as it allows us to detect meaningful differences in substance use outcomes between the GRIT intervention and the control group.

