### Data Analysis Plan

Baseline characteristics will be summarized using descriptive statistics to assess group balance. Primary analyses will follow the intention-to-treat principle, with all randomized participants included. Changes in adolescent alcohol and cannabis use will be compared between study arms using generalized linear mixed models (GLMMs) to account for within-subject correlation over time. Alcohol and cannabis use will be dichotomized as no or occasional use versus regular use (weekly or more) to evaluate the intervention’s effect on preventing initiation of regular substance use. Statistical significance will be assessed using two-sided tests with an alpha level of 0.05.

Multilevel mediation analyses will be conducted to examine mechanisms underlying intervention effects, with youth and caregiver emotional regulation specified as primary mediators. Additional exploratory mediators will include heart rate variability, psychological and cognitive flexibility, youth health behaviors (HRV biofeedback practice, sleep, nutrition, physical activity), and environmental factors (parental monitoring, family functioning, and caregiver substance use). Indirect and direct effects will be estimated using residual-based bootstrap methods to generate 95% confidence intervals. Sex differences will be evaluated in secondary analyses by including a sex-by-intervention interaction term.

Our primary analysis will be performed using mixed effects analysis, which provides unbiased estimates when missing data is missing at random (MAR). We will also consider multiple imputations to handle missingness using the Rubin method implemented in R package mice (53,54).

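### The trial is sized on an equal 0.025 split with no step-down test named; Holm would be more powerful at the same overall 0.05, by an amount that depends on the true power

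*Protocol article*

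**What the plan says.** Three places in the protocol article bear on this point.

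- **Power and Sample Size** gives the sizing basis as "80% power at a nominal alpha of 0.025 for each outcome (adjusted for multiplicity to achieve an overall alpha of 0.05 for both outcomes"). The resulting size is "a sample size of 105 dyads per arm (total N = 210 dyads"). The control-arm rates are given as follows: "we conservatively assumed a 20% initiation for alcohol and 8% for cannabis for our high-risk study population". The target is a 40% reduction in each.
- **Data Analysis Plan** says: "Statistical significance will be assessed using two-sided tests with an alpha level of 0.05". It does not repeat the split and names no procedure for the two primary outcomes.
- **Study Design and Study Aims** hypothesises that "adolescents who receive GRIT will have lower rates of regular alcohol and cannabis use compared to those in the active control group", so an effect is expected on both substances.

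No section mentions a step-down rule or any passing of alpha from one outcome to the other.

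**The concern.** The equal split is the only multiplicity rule in the document. Carried into the final analysis unchanged, it would hold each outcome to 0.025 even when the other had already been shown. Holm's procedure tests the smaller p-value at 0.025 and, if that is significant, the other at 0.05. It has the same overall error guarantee and rejects whatever the split rejects.

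The split gives up most when both effects are real, and that is what this trial hypothesises. At stake is power that could be had without recruiting more dyads or accepting more false positives. The analysis section's unsplit 0.05 adds a second reason to name the procedure: as written, a reader cannot tell which rule will decide the primary outcomes.

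**Working it through.** **Inputs from the protocol article.** Alpha 0.025 per outcome and 0.05 overall; 80% power for each outcome; 105 dyads per arm; 20% attrition; variance inflation 1.4; control rates 20% and 8%; 40% reduction, giving 20% vs 12% and 8% vs 4.8%; two-sided tests.

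**Assumption.** The correlation ρ between the two test statistics is not given, so a range is shown.

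**1. The plan's own figures.**
- Alpha: 0.025 + 0.025 = 0.05, as stated. With independent tests the exact overall error is 1 − 0.975² = 0.0494.
- Sample size: the standard two-proportion formula (two-sided 0.025, 80% power, no continuity correction) gives 398 per arm for alcohol and 1,111 for cannabis, before attrition and variance inflation. It does not reproduce 105. The sizing used a longitudinal mixed-model tool whose correlation and variance inputs are not shown, so this does not by itself prove 105 wrong. Steps 3 and 4 take the stated 80% as given; step 5 shows what happens without it.

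**2. Error control of Holm.** If neither outcome has an effect, a false claim needs the smaller p-value to be at most 0.025, which has probability at most 0.025 + 0.025 = 0.05. If exactly one has no effect, a false claim needs its own p-value to be at most 0.05. The overall error is therefore at most 0.05 under any correlation. Simulation with 2 million draws under no effect on either gave 0.0495 (ρ = 0), 0.0480 (0.3) and 0.0467 (0.5).

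**3. Power if both outcomes have the stated 80%.**
- Critical values: 2.241 at two-sided 0.025 and 1.960 at 0.05.
- Drift per outcome = z(0.9875) + z(0.80) = 2.241 + 0.842 = 3.083.
- Power at an unsplit 0.05 = Φ(3.083 − 1.960) = 86.9%.
- Holm power for outcome 1 = P(Z₁ > 2.241) + P(1.960 < Z₁ < 2.241 and Z₂ > 2.241). At ρ = 0 this is 0.80 + (0.869 − 0.80) × 0.80 = 0.855.
- Both significant at ρ = 0: split 0.80² = 0.640; Holm 0.8693² − 0.0693² = 0.751.

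| ρ (assumed) | Per outcome, split | Per outcome, Holm | Both, split | Both, Holm |
|---|---|---|---|---|
| 0 | 80% | 85.5% | 64.0% | 75.1% |
| 0.3 | 80% | 85.0% | 66.6% | 76.6% |
| 0.5 | 80% | 84.6% | 68.7% | 77.8% |
| 0.8 | 80% | 83.7% | 72.9% | 80.4% |

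**4. Unequal power.** If alcohol has 80% and cannabis 30%, then for ρ from 0 to 0.5 Holm adds about 1 to 2 points for alcohol and 8 to 9 for cannabis.

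**5. Simple endpoint comparison at the stated rates.** Completers per arm: 105 × 0.80 = 84. Power at two-sided 0.025 = Φ{[(p₁ − p₂)√n − 2.241√(2p̄(1 − p̄))] / √(p₁(1 − p₁) + p₂(1 − p₂))}.
- Alcohol: Φ(−0.832) = 20.3%.
- Cannabis: Φ(−1.397) = 8.1%.
- Holm gain for alcohol at ρ = 0: (0.291 − 0.203) × 0.081 = 0.7 points, rising to 1.0 at ρ = 0.5.
- Holm gain for cannabis at ρ = 0: (0.132 − 0.081) × 0.203 = 1.0 point, rising to 2.1 at ρ = 0.5.
- With the variance inflation applied as well (84 / 1.4 = 60 per arm), the gains are 0.5 to 0.8 points for alcohol and 0.6 to 1.5 for cannabis.

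**6. The analysis section read literally.** Testing each outcome at an unsplit 0.05 gives an overall error of 1 − 0.95² = 0.0975 with independent tests. Against that rule Holm is stricter: at ρ = 0, per-outcome power is 85.5% instead of 86.9%.

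**The case against.** The sentence on 0.025 is a sizing statement. It does not say how the final p-values will be judged, and sizing at 0.025 is equally the first step of Holm. A reader might infer that the plan commits to testing the second outcome at 0.025 after the first has been rejected; no section says so. The testing procedure may also be fixed in an analysis plan that is not shown, and its absence from an article is not a fault. Read literally, the analysis section's 0.05 would make Holm a restriction and not a gain. Finally, an equal split is valid, treats the two substances alike and gives simple simultaneous intervals.

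All of this stands, and it limits the point in three ways. The comparison with the split is conditional on the split being the final rule. The change belongs in the Data Analysis Plan and leaves the sizing sentence as it is. The point is one of efficiency.

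It does not remove the point. The split is the only multiplicity rule the article states, and the analysis section's alpha does not say whether it applies per outcome or overall. Naming Holm improves on either reading: it adds power if the split was meant, and it protects the overall error if an unsplit 0.05 was meant.

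**Conclusion.** The point holds as a conditional efficiency improvement. If the equal split is the final testing rule, Holm is at least as powerful in every case at the same overall 0.05. Per outcome, the gain is 3.7 to 5.5 points for correlations from 0.8 to 0; for showing both effects it is about 7 to 11 points. These figures rest on both outcomes truly having the stated 80% power and on an assumed correlation.

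A reader might take a gain of about 5 points per outcome as established. The documents do not support that. With 84 completers per arm and the stated rates, a simple endpoint comparison leaves only about 1 point for alcohol and 1 to 2 for cannabis. That comparison does not disprove the stated 80%, because the longitudinal sizing inputs are not shown, but the gain cannot be quoted without the condition. Nor should a reader infer that the split itself is a mistake: it controls the overall error as the sizing section says.

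**What to change.** In the Data Analysis Plan, state that the two primary outcomes are tested by Holm's procedure: the smaller of the two p-values at two-sided 0.025 and, if it is significant, the other at two-sided 0.05. Claim an effect only for the substance or substances that pass. Keep 0.025 in Power and Sample Size as the conservative sizing case. Make the change before any unblinded outcome data are seen.

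The same sentence settles how the analysis section's 0.05 relates to the sizing section's 0.025. No dyads, visits or measures change. The one small cost is that confidence intervals matching a step-down test are less simple than those matching the equal split.

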
### Sampling

Two hundred and ten adolescent-caregiver dyads (N=420), with adversity-impacted youth aged 11–14, will be recruited. Adolescents are considered adversity-impacted if they score in the high-risk category (4 or more ACEs or any number of ACEs and an ACE-related condition [e.g., school difficulties, symptoms of anxiety and/or depression]). Youth will be recruited from schools, health clinics, and youth-serving community organizations in Southern California. Eligible participants will be randomly assigned to either the GRIT intervention or the active control intervention (i.e., Digital Literacy).

Inclusion criteria for youth include: 1) being aged 11–14 years and scoring in the high-risk category on the ACEs and Toxic Stress Risk Assessment Algorithm; 2) having access to a smartphone and willingness to download an app if randomized to the GRIT intervention; and 3) have a positive, supportive adult such as a parent/guardian/primary caregiver aged 18 years or older who is English or Spanish-speaking and willing to participate in the intervention. The inclusion criteria for caregivers require them to be willing to engage in the intervention alongside the youth participant.

Exclusion criteria for youth participants include: 1) reporting alcohol or cannabis use within the last 14 days; 2) currently being enrolled in another family-based intervention (e.g., family therapy); 3) being in acute distress and requiring immediate care (e.g., imminent risk of harm to self or others, active psychosis); 4) requiring supervised visits by the Department of Children and Family Services (DCFS) with the identified caregiver; and 5) cases where the parent/guardian/primary caregiver declines participation, in which case the family will referred to other community-based programs.

### Recruitment Strategy

Black and Hispanic/ Latinx populations in California are more likely to have experienced 4 or more ACEs (32). As such, we will ensure that youth who self-identify as Black or Hispanic/ Latinx are well-represented in our sample by recruiting from diverse settings across Southern California. Recruitment for this study will leverage established relationships with schools, health care providers screening for Adverse Childhood Experiences (ACEs), especially in federally qualified health and school-based health centers, and community organizations serving adversity-impacted youth. While participant enrollment will come from these strong partnerships, the entire research team will also continue to foster relationships with additional schools and youth-serving organizations through community service (e.g., volunteering, board service), educational workshops, and tabling at community events.

### Recruitment Procedures

The research team will enroll each dyad in a staggered and overlapping manner. This strategy ensures that some participants will be in the consent and data collection process while others progress through various stages of the intervention. Enrolling at a rate of 4–8 dyads/month will allow us to reach our recruitment goal of 210 dyads. To inform potential participants, an IRB-approved flyer describing the study will be distributed to both the youth and their caregivers by our community partners. A scannable QR code linking to an online interest and eligibility form on REDCap will be provided for dyads to express their interest in the program. This form will collect contact and eligibility information to allow the research team to follow-up, share more information about the study, and confirm eligibility. The research team will use the Pediatric ACEs and Life Event Screener (PEARLS) to assess if the adolescent qualifies for the high-risk category based on their ACE score. PEARLS collects data on the number of ACEs the adolescent has experienced and identifies any recent ACE-associated conditions. Following eligibility screening, informed assent will be obtained from the youth and informed consent from the youth’s legal guardian (for youth participation) and the caregiver before enrollment. Participants will be given up to 72 hours to ask questions and decide about their participation. Once eligibility is confirmed, the baseline assessment will be scheduled, where the informed consent process will be finalized.

### Randomization

Eligible participants will first be stratified by ethnicity and ACEs scores, and then randomly assigned to one of the two study groups (GRIT Intervention or Digital Literacy Active Control) using a 1:1 ratio. Randomization will be performed using the REDCap randomization module, which will facilitate the computerized random allocation of dyads. Prior to study initiation, random allocation tables will be generated based on ethnicity and ACEs score (1–3 vs. 4 or more) using a custom R script. All research staff will remain blind to the randomization tables, which will be uploaded into REDCap for automatic allocation of dyads to study arms. After the baseline assessment, the research team will notify the project coordinator, who will verify the random assignment in REDCap.

### Enrollment Procedures

Once participants, both youth and caregiver, are jointly identified as eligible by the initial screener form, both caregiver and youth are automatically emailed a response through the REDCap system. This email contains instructions about the participant’s next steps for enrollment, as well as a link to a Bookings page where they may select a date for their initial baseline assessment. Within 48 hours of a confirmed eligible screening, the assessment team will use a phone/email script to either confirm a date, if provided in the screener, or set a date for the initial baseline assessment. Once both date and time are determined, the assessment team will help the interested dyad identify a quiet and accessible location (e.g., university space, home, library, local center) at which the assessment will be held. The assessment team then sends out confirmation for the baseline assessment via email and text message. This confirmation contains the location, date, time, and essential reminders for them not to eat a heavy meal, exercise, or drink caffeine or other stimulants 60–90 minutes before the assessment in preparation for the heart rate variability (HRV) assessment. This email will also contain two versions of the consent form, one in English and one in Spanish, for review at least three days prior to the baseline assessment. Two more reminder emails will be sent the day prior to the assessment and the morning of the baseline assessment with the same content as the initial confirmation email, confirming the appointment. Official enrollment begins at the baseline assessment. Once the dyad arrives at the designated location for their appointment, the enrollment team guides the dyad through the informed consent form and verbally quizzes both participants on sections detailing timeline, risk, and data privacy to ensure a thorough understanding of what their assent/consent and participation in the study entail. Once participants express a thorough understanding of the study and electronically sign the consent forms, the assessment procedures, including an HRV assessment, biometric measurements, and various self-report questionnaires, begin. In order to randomize the dyad into one of the two arms of the study, data from the youth’s initial screener and demographics survey will be extracted for randomization. When randomization occurs, dyads are officially enrolled into either the Digital Literacy or the GRIT arm of the study and given the corresponding materials for that program. Dyads are not blinded from their assignment into one of the two interventions; their assigned health coaches, however, are blinded to all collected data during the dyad’s assessments.

### Retention Strategies

#### Incentives.

Dyads receive a monetary incentive for completing their data collection measures. Both the youth and caregiver are compensated with a $50 Amazon e-gift card for completing each assessment at baseline, post-intervention, 6-month post-intervention, and 12-month post-intervention. If dyads are unable to complete an in-person data collection where we conduct the HRV assessment and collect anthropometrics, but at least complete the online surveys, they receive a $25 Amazon e-gift card. Additionally, a monthly competition is held for dyads randomized to the GRIT arm, in which individuals and dyads with the highest average of minutes practiced using their Inner Balance trainer receive a bonus $10 Amazon e-gift card. This bonus reward is to encourage engagement in the self-regulation techniques using biofeedback outside of the intervention session time.

#### Reminders.

A variety of contact information is obtained from the youth and caregiver, to ensure that contact is maintained throughout the 14-month study period. Phone number, e-mail, mailing address, social media handles, and emergency contact information are collected in addition to preferred methods of contact. Dyads receive both emails and text message reminders the day before and day of data collection assessments and intervention sessions.

#### Mobile Assessments.

Dyads are given the opportunity to choose the time and location for their data collection visit, such as their homes and local public spaces. To be considerate of work and school schedules, evenings and weekends are included as possible appointment options for assessments to occur. With the exception of the baseline assessments, dyads are also able to access and complete the online surveys ahead of their in-person assessment for the duration of the in-person visit. There is no in-person visit for the 6-month post-intervention assessment.

### Format and Session Delivery

Sessions are approximately 60 minutes in length and delivered weekly over an eight-week period. Over the course of 8 weeks, families participate in six core sessions once a week, followed by a booster session approximately six months later. Sessions are designed to be delivered online in a three-person interactive model involving a youth-caregiver dyad and a trained Community Health Worker (CHW). A bilingual CHW is available to conduct each session in English and/or Spanish. Each session is conducted live via a secure video conferencing platform and lasts approximately 60 minutes. Sessions include interactive lesson slides, real-world scenarios, and worksheets that are completed in real time during the session. These in-session activities are designed to reinforce core concepts and support the development of healthy habits. Each session concludes with a lesson review. The lesson review is led by the CHW, assessing if the dyad understood the content and providing space to clarify any questions on the concept.

Each session is facilitated by a Community Health Worker (CHW) trained in adolescent engagement and the delivery of structured, skills-based interventions. Using a standardized lesson plan guide and slides. The CHW guides the dyad through each lesson, encouraging real-time participation using verbal responses and worksheet activities. The materials are written at a middle school reading level and available in both English and Spanish. CHWs foster a safe and supportive environment that encourages honest discussion, while avoiding being clear about their role as a coach and not a therapist.

